**Methods/design:**

90 patients aged between 16 to 60 years, who meet the diagnostic criteria for CFS and have been diagnosed by their medical practitioner, will be randomly recruited into groups consisting of Intermittent exercise, Graded exercise and usual care (Control). The outcomes will be measured pre-study (Week 0) and post-study (Week 13). Primary outcomes are VO_2peak_, anaerobic threshold, peak power, levels of fatigue, immune cell (CD3^+^CD4^+^, CD3^+^CD8^+^, CD19^+^, CD 16^+^CD56^+^) concentrations and activation. Secondary outcomes include onset of secondary CFS symptoms (e.g. fever, swollen lymph nodes), wellness, mood and sleep patterns. Primary analysis will be based on intention to treat using logistic regression models to compare treatments. Quantitative data will be analysed using repeated measures ANOVA with a linear model, and Cohen’s effect size. Qualitative data such as participants’ responses (e.g. changes in mood and other reactions) following the exercise modalities will be read and sections demarcated. A code will be applied to each segment. A prevalence of codes will be considered thematically.

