### Sample size and power calculation

A previous exercise intervention study provided VO_2peak_ data from a CFS sedentary, age-matched cohort (16.2±1.3 yr) [18]. This data has been used to compute statistical power *a priori* using the non-commercial statistical power analysis program G*Power. The control group is expected to experience no change in the aerobic capacity after 12-weeks while the intervention groups are expected to increase this measure following the exercise interventions. Setting an alpha level of 0.05, approximately 75 participants (25 per group) will provide 82% power to detect a statistically significant difference between groups. Recruitment will be inflated to 90 participants to enable a 20% participant attrition rate.

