### Participants

The inclusion criteria for the study are a medical diagnosis of CFS from the participant’s medical practitioner, according to CDC criteria; an age range of 16 to 60 yr; no diagnosed cardiorespiratory, endocrine, metabolic condition or current musculoskeletal injury that would make exercise participation hazardous; the ability to communicate in English; provision of informed consent; willingness to participate in three exercise sessions per week. Participants will be recruited from the local community through advertisements at the Southern Cross University campus and Health Clinic, local medical clinics and hospitals, local newspapers, television and radio media. Participants will be randomized *via* computer-generated randomly permuted blocks stratified by gender and age (< 40 years; > 40 years) into the intervention groups and control group. A university employee not involved in exercise testing or delivery of the intervention will prepare the randomization assignments. Group assignment will be delivered to participants in sealed envelopes upon the completion of baseline testing. Participants who have been randomized into the control group will be offered a supervised 12-week exercise program upon completion of the study.

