### Outcome measures

All outcome measures will be collected at baseline (Week 0) and after the exercise interventions (Week 13). Trained research personnel blinded to the randomization procedures will conduct the initial participant screenings and baseline assessments, which include a full medical history, resting heart rate, resting blood pressure and anthropometry (height; weight; BMI; waist, hip and limb girths), fatigue severity and wellness questionnaires. The project outcome measures consist of a full cell count; lymphocyte receptor flow cytometric assays; incremental cycling test (VO_2peak,_ anaerobic threshold); spirometry; Personal Well Being Index [33] and Fatigue Severity Scale [34].

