### Statistical analyses

Primary analysis will be via intention-to-treat with all patients included regardless of dropout or level of adherence. Missing data will be imputed according to the maximum likelihood expectation algorithm via the Statistical Package for the Social Sciences (SPSS© Version 19.0). Physiological and exercise test data will be presented as the mean ± standard deviation, with confidence intervals used to express group differences. Changes between groups and the time effect for each group will be determined by repeated measures analysis of variance with a Bonferroni adjustment for significant differences between groups. Cohen’s Effect sizes and 90% confidence intervals will be calculated, to utilise a magnitude-based approach to inferences [41], with the following descriptors applied: (1) Effect size thresholds: <0.2 trivial, <0.6 small, <1.2 moderate, <2.0 large, <4.0 very large, >4.0 extremely large, and (2) Thresholds for assigning qualitative terms to chances of substantial effects: <0.5%, almost certainly not; <5.0%, very unlikely; <25%, unlikely; <75%, possible; >75%, likely; >95%, very likely; >99.5%, almost certain. An effect is unclear if its confidence interval includes both substantial increases and decreases [41]. A p value of < 0.05 will be considered indicative of statistical significance; clinical significance will be interpreted in light of the meaningfulness and magnitude of the adaptations observed. Data from linear pain scales will be recorded pre- and post-study, and reported as frequencies of scores between 0 and 10. Data will then be analysed using ANOVA (group and time effects). Data from wellness indices will be recorded pre and post, combined into domains and a representative total score from the time points analysed using an ANOVA. Data (non parametric) from the Fatigue scales, also measured at time points, will be collated and analysed using a Kruskall-Wallis test.

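### The abstract's primary logistic regression has no binary primary outcome and no counterpart in the Methods; for continuous outcomes, baseline adjustment would be more efficient than the two-time-point repeated-measures ANOVA

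*Protocol article*

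**What the plan says.** The abstract (Methods/design) states: "Primary analysis will be based on intention to treat using logistic regression models to compare treatments". Its next sentence reads: "Quantitative data will be analysed using repeated measures ANOVA with a linear model, and Cohen’s effect size".

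The Statistical analyses section opens with "Primary analysis will be via intention-to-treat with all patients included regardless of dropout or level of adherence" and names no logistic model. For comparisons between groups it says "Changes between groups and the time effect for each group will be determined by repeated measures analysis of variance with a Bonferroni adjustment". Pain and wellness scores go to ANOVA. For fatigue, which both lists make a primary outcome, it says "Data (non parametric) from the Fatigue scales, also measured at time points, will be collated and analysed using a Kruskall-Wallis test".

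The Outcome measures section fixes two assessments: "All outcome measures will be collected at baseline (Week 0) and after the exercise interventions (Week 13". The Participants section describes randomisation by "computer-generated randomly permuted blocks stratified by gender and age (< 40 years; > 40 years". The sample size section says "Setting an alpha level of 0.05, approximately 75 participants (25 per group) will provide 82% power to detect a statistically significant difference between groups".

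**The concern.** A primary analysis has to fit the outcome it is applied to. Logistic regression needs a yes/no response, and the outcomes called primary are measured on continuous or ordered scales. If the abstract's sentence stands, someone must later either choose a cut-off, possibly with data in view, or drop the stated primary analysis.

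The second matter is efficiency. With two time points, the repeated-measures ANOVA compares changes from baseline. It does not fit baseline as a covariate, and no named analysis includes the two factors used to stratify randomisation. Precision that the collected data could supply goes unused.

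**Working it through.** **1. Outcomes against the stated model.**

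- Abstract, primary: VO2peak, anaerobic threshold, peak power, fatigue, and immune cell concentrations and activation.
- Design section, primary: VO2peak, perceived exertion, fatigue, muscle pain, and immune cell counts, concentrations and function.
- All of these are continuous or scale measures, and no section defines a responder threshold.
- The clearest candidate for a yes/no outcome is symptom onset, which the abstract lists as secondary. The Statistical analyses section gives it no method.

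So the logistic model named as primary has no primary outcome to act on.

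**2. What the repeated-measures ANOVA tests.** With Week 0 and Week 13 only, the group-by-time F test is identical to a one-way ANOVA of the change score. Baseline is used, but with its coefficient fixed at 1 instead of estimated.

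**3. Relative efficiency.** Let σ² be the common variance at both times and r the pre-post correlation. The document gives neither, so equal variances and the values of r are assumptions.

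- Change score: variance 2σ²(1 − r)
- Week 13 value adjusted for baseline: variance σ²(1 − r²)
- Ratio: (1 − r²) / [2(1 − r)] = (1 + r)/2

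**4. The plan's own figure.** The 82% at 25 per group cannot be reproduced, because the document gives no difference, standard deviation, effect size, correlation or named test. It can only be solved backwards. A three-group F test with 2 and 72 degrees of freedom at alpha 0.05 has 82% power when the noncentrality is λ = 10.55. That is f = √(10.55/75) = 0.375 on the scale of the analysed variable. The figure is neither confirmed nor refuted.

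**5. Power after adjustment.** Suppose the 82% refers to the group-by-time test. Divide λ by (1 + r)/2 and use 75 − 3 − 3 = 69 error degrees of freedom (baseline, gender and age stratum each cost one).

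| assumed r | variance ratio | λ | power at N = 75 | N equivalent to 75 (75 × ratio) |
|---|---|---|---|---|
| 0.5 | 0.75 | 14.06 | 91.8% | 56 |
| 0.7 | 0.85 | 12.41 | 88.0% | 64 |
| 0.8 | 0.90 | 11.72 | 86.0% | 68 |
| 0.9 | 0.95 | 11.10 | 84.0% | 71 |
| 0.95 | 0.975 | 10.82 | 82.9% | 73 |

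These powers are for the overall three-group comparison, not for each Bonferroni-adjusted pair.

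**6. Simulation check.** In 5,000 replicates per setting, with both exercise groups shifted equally and adjustment for baseline only, change score against adjusted analysis gave 82.1% and 91.6% at r = 0.5, 81.0% and 84.6% at r = 0.8, and 81.3% and 83.7% at r = 0.9. This agrees with the formula to within simulation error.

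**7. Cost of the stratum terms.** Adding the two stratification terms alone, if they predict nothing, moves power from 82.0% to 81.95%.

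**8. Age strata.** Eligibility runs from 16 to 60 years, and the strata are below 40 and above 40. An eligible participant aged exactly 40 has no stratum.

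**The case against.** The strongest reply is that the conflict is one stray sentence in an abstract. That sentence is followed at once by another giving quantitative data to repeated-measures ANOVA, as the Statistical analyses section does. A reader might infer two rival models for VO2peak; the documents do not support that. Logistic regression might also have been meant for symptom onset, so striking it out altogether could remove a legitimate secondary analysis. Both points stand, and the remedy allows for them. They do not rescue the abstract's statement that the logistic model is the primary analysis.

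The reply on efficiency is that a change-score comparison is valid under randomisation, so preferring covariate adjustment is an improvement and not the correction of an error. That also stands. A reader might infer that the plan ignores baseline; it does not, because the group-by-time test works through change.

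On stratification, a condensed article may leave covariates to a fuller document, so its silence is not a defect in itself. A reader might infer that omitting gender and age makes the standard errors too wide. That follows only if these factors still predict the outcome once baseline is accounted for, which the document does not show.

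Finally, a reader might expect one adjusted model to settle the whole analysis, with an assured gain in power. It does not settle which outcomes are primary: anaerobic threshold, for example, is primary in the abstract and secondary in the Design section. It also leaves fatigue assigned to a rank test. The gain depends on an unstated correlation and on an unstated test behind the 82%.

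**Conclusion.** The contradiction is established from the text alone: the analysis called primary in the abstract fits no primary outcome and is absent from the Methods. It must be reconciled.

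For continuous outcomes the two places agree, and the method they name is valid but not the most efficient. The gain from baseline adjustment runs from about 10 percentage points at a correlation of 0.5, through 4 at 0.8, to about 2 at 0.9 and 1 at 0.95. It assumes equal pre and post variances and that the 82% describes the group-by-time test. The direction of the gain is firm under equal variances; its size is not known from the document. The stratum terms are an inexpensive addition that may or may not help. The gap at age 40 is real but minor.

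**What to change.** - **Reconcile the abstract with the Statistical analyses section.** Remove logistic regression as the primary analysis, or state that it applies only to a named, defined binary secondary outcome such as symptom onset.
- **Continuous outcomes such as VO2peak.** In both places, specify a linear model for the Week 13 value with treatment group, baseline value, gender and age stratum. Report the three pairwise adjusted differences with Bonferroni-adjusted confidence intervals.
- **Separately, reconcile the two primary-outcome lists** and decide how the fatigue scales, now assigned to Kruskal-Wallis, fit with the rest of the primary analysis.
- **Define the age strata as <40 and ≥40.**

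The cost is wording and about three error degrees of freedom. Every covariate is already collected, and no further participants or measurements are needed.

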Strategies to manage CFS include pharmacology, physical activity where appropriate (for example graded exercise (GE) and pacing), and psychological approaches such as cognitive behavioural therapy (CBT) which seek to modify behaviour, beliefs and coping strategies. [17-20]. Current best practice for the physical training of CFS patients involves GE sessions where the patient exercises at a well-tolerated constant rate or load (steady state), and the duration of the exercise session is gradually increased over time [2,18-20]. CBT is usually combined with exercise management [18,20].

Evidence of the efficacy of GE, CBT, pacing and other prescriptions of physical activity has been mixed. Some CFS patients still report symptom exacerbation and muscle pain with GE, and consequently are less likely to be physically active [21,22]. Yet other studies have reported that aerobic and resistance exercise improves aerobic capacity and strength [13], fatigue [17], profile of mood states and inflammatory cytokines [14,17,21,23-26].

Intermittent training, where intervals of exercise are alternated with intervals of rest or very low intensity exercise, has been used with cardiac [27], pulmonary [28,29], cancer [30] and older clients who are very deconditioned [31]. Clapp et al. (1999) reported that an acute session of intermittent exercise for 30 minutes did not exacerbate CFS symptoms immediately post-exercise, or for up to 7 days post exercise [32]. In CFS patients, intermittent training may increase exercise tolerance by decreasing perceived exertion, and delaying the onset of fatigue and muscle pain, whilst still providing the same total amount of physical activity as GE. Patients may find it easier to adhere to an intermittent exercise programme if their symptoms are not exacerbated, and therefore may improve their health.

Study hypotheses and aims: the primary aim of the trial is to investigate the efficacy of 12 weeks of intermittent or graded exercise on aerobic capacity, fatigue, immune function and wellness in CFS patients compared to standard care (typically rest, pharmacology and advice about physical activity). We hypothesise that:

1) Both exercise interventions will improve exercise tolerance, aerobic capacity and wellness compared to the control condition, and

2) IE will result in greater exercise tolerance, less fatigue and other symptoms, improved immune function and better exercise adherence compared to GE.

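### With exactly three arms, the Bonferroni adjustment of the arm comparisons is valid but more conservative than needed; a Shaffer step-down or a gated closed test keeps familywise error at 5% and gains power

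*Protocol article*

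**What the plan says.** The trial compares three arms: "groups consisting of Intermittent exercise, Graded exercise and usual care (Control"). Under Statistical analyses, changes between groups are to be assessed by "repeated measures analysis of variance with a Bonferroni adjustment for significant differences between groups", and "A p value of < 0.05 will be considered indicative of statistical significance". The divisor is not stated. The same section sends the fatigue scales to a Kruskal-Wallis test and the pain and wellness data to ANOVAs for which no Bonferroni adjustment is named. It also plans 90% intervals for effect sizes, again with no adjustment named.

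The hypotheses at the end of the Background set each exercise arm against control ("Both exercise interventions will improve exercise tolerance, aerobic capacity and wellness compared to the control condition") and then intermittent exercise (IE) against graded exercise (GE). Together these are the three pairwise comparisons. The sample size section sizes the trial on VO2peak: "Setting an alpha level of 0.05, approximately 75 participants (25 per group") are said to give 82% power. It names neither the test behind that figure nor an effect size or SD, and it mentions no adjustment.

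**The concern.** The article itself names the multiplicity rule for the arm comparisons, so this is a stated choice and not a detail left to a fuller document. Bonferroni protects against every way in which several null hypotheses could be true at once. With three arms there are few such ways. If any two of the three pairwise nulls are true, the third is true as well, so the number of true pairwise nulls is three, one or none, and never two. Bonferroni keeps dividing alpha by three even when at most one null can still be true. At stake is the chance of showing, with 25 participants per arm, that the exercise arms differ from control on VO2peak and the other exercise-test variables.

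**Working it through.** **Inputs from the protocol article.** Three arms; 25 per arm, 75 in total; alpha 0.05; stated power 82% ("will provide 82% power to detect a statistically significant difference between groups"); expected pattern of control unchanged and both exercise arms rising.

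**Assumptions, because the article is silent.** Two-sided tests; a Bonferroni divisor of 3, so 0.05/3 = 0.0167 per pair; equal rises of d SD in both exercise arms; normal change scores with a common SD; complete data. With two time points, the group-by-time test is the one-way F test on change, with 2 and 72 df.

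**The plan's own figure.** The 82% cannot be reproduced without an effect size, so it is inverted.
- Read as omnibus power: 82% at N = 75 needs a noncentrality of 10.55, so f = √(10.55/75) = 0.375. For means (0, d, d) the deviations from the grand mean are −2d/3, d/3 and d/3. Their mean square is 2d²/9, so f = d√2/3 and d = 0.375 × 3/√2 = 0.795.
- Read as the power of one pairwise t-test at 0.05 with 25 per arm: d = 0.83.

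**Why the alternatives control the error.** In the closed family of pairwise hypotheses, the only intersection is that all three arms are equal. The omnibus F test tests that at 0.05. Once it rejects, each pair may be tested at 0.05 with strong familywise control. Shaffer's step-down uses the same logic without the F gate: the smallest p is compared with 0.05/3 and, if rejected, the other two with 0.05. It therefore keeps every Bonferroni rejection.

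**Familywise error by simulation** (at least 200,000 trials per setting, pooled SD, 72 df).

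| Rule | All arms equal | One true null pair, other arm at d = 0.795, 0.83 or far away |
|---|---|---|
| Bonferroni | 4.3% | 1.6–1.7% |
| Closed test | 4.9–5.0% | 4.9–5.1% |
| Unadjusted, no gate | 12% | about 5% |

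The 5.1% is within simulation error of 5%.

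**Chance that both exercise arms beat control.**

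| d | Bonferroni | Shaffer | Closed test |
|---|---|---|---|
| 0.4 | 6% | 12–13% | 14% |
| 0.795 | 49% | 65% | 67% |
| 1.2 | 93% | 97% | 97.5% |

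Holm's step-down gives 56% at d = 0.795, a smaller gain. Adding an F gate in front of Bonferroni leaves the 49% unchanged. On the pairwise reading, d = 0.83, the figures are 54% for Bonferroni, 61% for Holm and 72% for the closed test.

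**Each exercise arm against control, d = 0.795.** Bonferroni 64%, Shaffer 72%, closed test 75%.

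**IE against GE.** The article states no expected size for this contrast, so this is illustration only. With control, one exercise arm and the other equally spaced at 0, 0.415 and 0.83 SD, power is 17% with Bonferroni and 29% with the closed test.

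**The case against.** - **Bonferroni is valid.** This stands. The section states nothing false here, and the point concerns efficiency only.
- **Bonferroni buys something.** A reader might infer that power is lost for nothing. The documents do not support that. The article wants confidence intervals to express group differences, and Bonferroni intervals match Bonferroni tests. Under the gate, a 95% interval may exclude zero while no claim is allowed. The article does not ask for simultaneous intervals, so this is a real cost but not a breach of a stated aim. In addition, if IE and GE truly do not differ, the chance of claiming that they do rises from about 1.6% to at most 5% per outcome.
- **Several primary outcomes.** The Design section lists many, and no adjustment across them is stated. That is a separate matter that neither rule addresses, but a less strict rule between arms makes it more visible.
- **The size depends on d.** This stands. The gain for both arms is about 6 to 8 points at d = 0.4, 16 to 18 at 0.795 and about 4 at 1.2. The largest figure should not be quoted alone.
- **Limited scope.** A reader might infer that both hypotheses are decided by these tests. They are decided only in part. Wellness, pain and the fatigue scales have other analyses with no Bonferroni named.
- **Dominance.** The closed test does not strictly dominate ungated Bonferroni: in at most 0.5% of simulated trials Bonferroni rejected a pair that the gate would have blocked. Shaffer does dominate it.

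**Conclusion.** The point holds as a cheap improvement. For the outcomes under the repeated measures ANOVA, Bonferroni can be replaced by a rule with the same 5% familywise guarantee and more power. At the effect implied if the 82% is omnibus power, the chance that both exercise arms beat control goes from 49% to 65% (Shaffer) or 67% (closed test). The gain is smaller for weak and for strong effects. All power figures rest on the assumed divisor of 3, 25 per arm, equal rises in both exercise arms and a back-solved or chosen d.

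Two stronger readings are not supported.

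1. A reader might infer that the adjustment contradicts the stated 82%. If that figure is pairwise at 0.05, the same d = 0.83 has about 67% power at 0.0167. If it is omnibus power, a later pairwise adjustment does not touch it. The article does not say which.
2. A reader might take the wording of the first hypothesis as a formal requirement that both comparisons succeed, which would need no split of alpha. No section defines success that way.

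**What to change.** Under Statistical analyses, replace the Bonferroni wording for these outcomes with: 'Pairwise comparisons of change between arms are made only if the three-arm group-by-time test is significant at 0.05, and each is then tested at 0.05 (closed testing, three arms).' If no gate is wanted, name Shaffer's step-down instead: the smallest p-value against 0.05/3 and, if that is rejected, the other two against 0.05. One of these must be kept, because unadjusted pairwise tests with no gate give about 12% familywise error when all arms are equal. The wording is specific to three arms.

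The change is one sentence and needs no further participants or data. In return, the intervals no longer match the tests as simply as Bonferroni intervals do, so the report should say that pairwise 95% intervals are unadjusted and that claims follow the testing rule. The higher false-claim rate for a truly null pair, at most 5% per outcome, has to be accepted.

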## Methods

### Design

This study is a randomised controlled trial that will compare the outcomes of a 12-week intermittent cycling exercise program to a graded exercise cycling program and standard care (rest and lifestyle advice). The primary outcomes of the study are aerobic capacity (VO_2peak_), perceived exertion, fatigue, muscle pain, immune cell counts, lymphocyte (CD4^+^, CD8^+^, CD19^+^, CD16^+^56^+^) concentrations and function. Secondary outcomes are wellness indices and physiological adaptations to exercise (changes in heart rate, heart rate variability, blood pressure, body composition, anaerobic threshold) and measures of presence, severity and type of fatigue (mental and physical). Southern Cross University Research Ethics Committee has approved all study procedures (HREC ECN-13-066).

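### The pain analysis names group and time effects but not the between-arm comparison of change that the hypotheses need; the group effect is a valid but diluted test

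*Protocol article*

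**What the plan says.** The Statistical analyses section of the protocol article treats pain separately from the other outcomes. It first sets the data: "Data from linear pain scales will be recorded pre- and post-study, and reported as frequencies of scores between 0 and 10". It then sets the test: "Data will then be analysed using ANOVA (group and time effects"). For pain it names no group-by-time term, change score or baseline adjustment.

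Earlier in the same section, directly after a sentence on physiological and exercise test data, a different wording is used: "Changes between groups and the time effect for each group will be determined by repeated measures analysis of variance", with a Bonferroni adjustment. The abstract also gives repeated measures ANOVA for quantitative data in general.

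On the status of pain, the Design section lists it as primary: "The primary outcomes of the study are aerobic capacity (VO_2peak_), perceived exertion, fatigue, muscle pain, immune cell counts". The abstract's list does not contain it: "Primary outcomes are VO_2peak_, anaerobic threshold, peak power, levels of fatigue, immune cell" and so on.

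The hypotheses at the end of the Background compare arms. The second is that "IE will result in greater exercise tolerance, less fatigue and other symptoms, improved immune function and better exercise adherence compared to GE".

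Wellness scores are to be "combined into domains and a representative total score from the time points analysed using an ANOVA", with no contrast named.

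**The concern.** With a score before and a score after treatment in three randomised arms, the hypotheses ask whether the arms changed differently. That is the group-by-time term or, better, a comparison of Week 13 scores adjusted for Week 0. The pain sentence names two other effects.

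- **Group main effect.** It compares arms on the average of Week 0 and Week 13. Allocation is disclosed only after baseline testing (Participants section), so Week 0 carries no treatment effect. The average therefore holds half of any Week 13 difference, and stable differences between people stay in the error term.
- **Time main effect.** It asks whether all participants together, controls included, changed. The Background says that symptoms fluctuate and that some patients improve over time, so a common drift is realistic.

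At stake is the pain result. An analyst who follows the sentence literally would use a weaker test of treatment than the same data allow, and would report next to it a time effect that says nothing about treatment.

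**Working it through.** **Inputs from the article.** Three arms, 25 per group (75 in all), alpha 0.05, stated power 82% (Sample size and power calculation); two study time points, Week 0 and Week 13 (Outcome measures).

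**Inputs assumed.** The article gives no effect size, SD or pre-post correlation for pain. I assume one pain score per study visit, equal SDs at both visits, a Week 13 shift of D = 0.8 SD in both exercise arms and none in control, and a pre-post correlation r from 0 to 0.7.

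**The article's own figure.** The 82% refers to VO2peak. It cannot be reproduced, because neither the effect size nor the test is stated; it can only be inverted. With 25 per group, 82% power needs f = 0.375 in a one-way ANOVA of three groups, or d = 0.81 in a two-arm comparison. A shift of 0.8 SD is therefore of the size that the trial is planned to detect.

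**Formulas.** Let S be the sum of squared deviations of the arm pattern (0, 1, 1) from its mean: S = 4/9 + 1/9 + 1/9 = 2/3. Each test is an F test with 2 numerator degrees of freedom and noncentrality λ:

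- Group main effect (average of the two visits; effect D/2, variance (1 + r)/2): λ = 25 × S × (D²/4) / ((1 + r)/2), 72 error df
- Group-by-time (change; effect D, variance 2(1 − r)): λ = 25 × S × D² / (2(1 − r)), 72 error df
- Baseline-adjusted Week 13 (effect D, variance 1 − r²): λ = 25 × S × D² / (1 − r²), 71 error df

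At D = 0.8, 25 × S × D² = 25 × 0.6667 × 0.64 = 10.67. At r = 0.5:

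- Group: (10.67/4)/0.75 = 3.56
- Group-by-time: 10.67/1 = 10.67
- Baseline-adjusted: 10.67/0.75 = 14.22

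**Power at D = 0.8 SD, 25 per arm**

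| r | Group main effect | Group-by-time | Baseline-adjusted |
|---|---|---|---|
| 0 | 51% | 51% | 82% |
| 0.3 | 41% | 68% | 86% |
| 0.5 | 36% | 82% | 92% |
| 0.7 | 32% | 97% | 99% |

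A simulation of 20,000 trials at r = 0.5 gave 35% for the group effect and 82% for group-by-time. With a smaller shift of 0.5 SD at r = 0.5, the figures are 16%, 42% and 53%.

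**Time main effect under drift.** Suppose that the arms do not differ and everyone changes by c SD. Then λ = 75 × c² / (2(1 − r)) with 1 and 72 df. At r = 0.5, c = 0.2 gives λ = 3.00 and significance in 40% of trials; c = 0.3 gives λ = 6.75 and 73%. Over r from 0.3 to 0.7 the ranges are 30% to 60% and 58% to 91%. The group and group-by-time tests stay at 5% under such a drift.

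**The case against.** The strongest reply is that the parenthesis lists the factors of the model and does not restrict the tests. The abstract's repeated measures ANOVA excludes no quantitative outcome, and the earlier sentence in the Statistical analyses section speaks of changes between groups without expressly confining itself to physiological data. A repeated measures model with a group factor ordinarily supplies the interaction, and a journal article can leave model terms to a fuller plan. This may well be what the authors meant. It does not settle the matter: the pain sentence is separate, drops both the repeated measures and the between-group change, and names two effects of its own.

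Three stronger readings are tempting, and the article does not support them.

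- *The named effects cannot detect a treatment difference.* Not so. Randomisation makes the expected Week 0 scores equal, so the group main effect is a valid test of treatment, only diluted.
- *A real difference would mostly be missed because of this rule.* That depends on a correlation and an effect size that the article does not give. At r = 0 nothing is lost against group-by-time. With D set so that group-by-time has 82% power, the group effect still has 54% at r = 0.3.
- *A common drift would yield a false claim of efficacy.* Only if the time effect were read as a treatment effect. The article nowhere says that it will be, and its hypotheses are all between arms.

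Two limits also stand. The status of pain as a primary outcome is itself inconsistent between the Design section and the abstract. And the wellness sentence most naturally means a total at each time point; it merely leaves the contrast unnamed.

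**Conclusion.** The point holds as a defect of specification. For an outcome that the Design section calls primary, the article names two effects and omits the comparison that its hypotheses need. Taken literally, the rule costs 27 points of power against group-by-time at correlation 0.3 (41% v 68%), 46 at 0.5 (36% v 82%) and 65 at 0.7 (32% v 97%), and nothing at 0. Against a baseline-adjusted comparison, the loss is 31 to 67 points over the whole range from 0 to 0.7. These sizes rest on the assumed 0.8 SD shift, 25 completers per arm, equal variances and approximately normal scores. If the sentence is shorthand for a group-by-time analysis, the loss against that term disappears, and what remains is wording that should say so. It should be corrected, but it does not show that the pain result would be wrong.

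**What to change.** In the Statistical analyses section, replace the group and time effects named for pain with one between-arm test: a comparison of Week 13 pain scores adjusted for Week 0 (ANCOVA) or, at the least, the group-by-time term of the repeated measures model. Follow it with Bonferroni-adjusted pairwise contrasts: IE v control, GE v control, IE v GE. State that the group and time main effects are descriptive only. Make the Design section and the abstract agree on whether muscle pain is primary. Naming the same contrast for the wellness scores is a clarification only.

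The cost is one or two sentences. The data are already to be collected, and no patients, visits or measurements are added.
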